### Patient recruitment and inclusion/exclusion criteria

Participating centres contribute to patient recruitment using a stepwise approach, with one centre initiating recruitment first and the other following in the second stage. All patients referred to an orthopaedic surgeon at the participating hospitals for assessment of the need for TKR are screened for eligibility and receive written information about the trial by post from an administrator before the appointment. Eligible patients (table 1) receive additional oral information and are invited to participate in the trial by a nurse involved in the appointment. The nurse obtains signed informed consent (online supplemental file 1) and delivers it to the trial coordinator (lead author). Time for consideration is offered if needed. An appointment for baseline measures and randomisation is scheduled by the trial coordinator. A visual representation of the trial timeline is shown in figure 1.

**Table 1 T1:** Inclusion and exclusion criteria

Inclusion criteria	Exclusion criteria
40–85 years at the time of surgery decision	Previous knee replacement in the other knee
Awaiting primary unilateral total knee replacement	Other reason than knee OA as the primary reason for surgery
Knee OA being the primary reason for surgery	Impaired cognitive function
Reside within 60 min travel time to the site of the intervention	Not fluent in written and spoken Swedish
	Chronic illness or disability, etc hindering full participation in the intervention

OA, osteoarthritis.

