### Randomisation

Patients are randomised using opaque, concealed envelopes and stratified by age (≤67 years, >67 years) with a 1:1 allocation ratio, based on computer-generated random number sequences, into the intervention group, comprising prehabilitation in addition to standard care (SC+P), or the control group, consisting of standard care only (SC). The computer-generated random number envelope sequences were created by a person not otherwise involved in the trial. Allocation is performed by the trial coordinator immediately after the baseline assessment. The trial coordinator did not have access to the randomisation lists before allocation.

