### Analysis plan

All analyses will be performed using IBM SPSS Statistics software, V.29, applying intention-to-treat and per-protocol approaches with an α-level of 0.05. Demographic data will be presented as mean or median with SD or IQR for quantitative variables, and as frequencies and percentages for categorical variables.

Depending on measurement scale and distribution, differences between groups at baseline and for primary and secondary outcomes at each follow-up assessment will be analysed using independent samples t-tests or non-parametric equivalent tests. Longitudinal changes within groups from baseline to follow-up time points will be analysed using linear mixed models or generalised linear models, with baseline measurements included as covariates. Multiple linear regression and logistic regression will be used to analyse predictor variables for the primary outcomes (FJS-12 and Mod-PEI-2). Furthermore, analyses of primary and secondary outcomes will be adjusted, if necessary, for differences in intervention delivery and adherence, duration of participation, surgical procedures and postoperative physiotherapy care.

Multiple analyses will be performed using α-level adjustment methods, such as the Bonferroni method. In the intention-to-treat analysis, a sensitivity analysis will be performed to quantify the magnitude of missing data from patients lost to follow-up. Appropriate statistical methods will be used to account for missing data in the analysis, depending on the characteristics of the missing data. If there is extensive missing data, a second table of baseline characteristics will be presented only for patients included in the final analysis. The proportion of missing outcomes per group, characteristics of patients with missing data and possible reasons for missing outcome data will be presented.

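### The stated between-group test ignores the baseline score and the age stratum, while the baseline-adjusted model is tied to within-group change

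*Protocol article*

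**What the plan says.** The Analysis plan of the protocol article gives each method a task.

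- **Between groups.** Differences in "primary and secondary outcomes at each follow-up assessment will be analysed using independent samples t-tests or non-parametric equivalent tests". No covariate is named.
- **Within groups.** "Longitudinal changes within groups from baseline to follow-up time points will be analysed using linear mixed models or generalised linear models, with baseline measurements included". Baseline thus enters these models as a covariate.
- **Predictors.** "Multiple linear regression and logistic regression will be used to analyse predictor variables for the primary outcomes (FJS-12 and Mod-PEI-2"). The treatment comparison is not mentioned here.
- **Conditional adjustment.** Analyses of primary and secondary outcomes may be "adjusted, if necessary, for differences in intervention delivery and adherence, duration of participation, surgical procedures and postoperative physiotherapy care".

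The Abstract puts between-group and within-group differences in one sentence with both families of method and does not say which method serves which comparison.

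Under Randomisation, allocation is "stratified by age (≤67 years, >67 years) with a 1:1 allocation ratio". Centre is not a stratification factor, and the two centres recruit in stages, "with one centre initiating recruitment first and the other following in the second stage". Table 3 shows that FJS-12 and Mod-PEI-2 are both collected at baseline.

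**The concern.** The aim is a between-group effect: prehabilitation added to standard care against standard care alone. As written, the model that uses baseline information serves a different question, namely how each arm changes over time. Both arms have the same operation, so both may well improve. A significant change in one arm and a non-significant change in the other is not evidence that the arms differ. The randomised contrast is left to a test that uses neither the baseline score nor the age stratum.

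What is at stake is precision and clarity. If the baseline score predicts the follow-up score, an unadjusted test gives away power that could be had from data already collected. If age is prognostic, stratifying by it and then leaving it out of the analysis makes the standard error too wide. Chance imbalance in the baseline score, or between centres, stays in the estimate. An adjustment made only if judged necessary also leaves the choice of primary estimate open until data are in hand, and the Strengths and limitations section states that the statistician is not blinded to allocation.

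**Working it through.** **Inputs.** From Sample size: FJS-12 difference 17.7 points, effect size 0.61, power 80%, α 5% (sidedness is not stated; two-sided assumed), dropout 20%, total 110. The baseline-to-52-week correlation r of FJS-12 is not given, so a range is shown.

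**Step 1: reproduce the plan's figure.** A two-sample t-test with d = 0.61, two-sided α 0.05 and power 0.80 needs 43.2 patients per arm, rounded up to 44. The total is 2 × 44 = 88 evaluable, and 88/(1 − 0.20) = 110. The target therefore matches an unadjusted two-sample t-test.

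**Step 2: implied SD.** 17.7/0.61 = 29.0 points. The article does not say whether this is the SD of the 52-week score or of the change. It is first taken as the SD of the 52-week score.

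**Step 3: effect of baseline adjustment.** With a linear baseline covariate, the residual SD is SD × √(1 − r²) and the standardised effect is 0.61/√(1 − r²). Power is for a two-sample t-test with 44 evaluable patients per arm.

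| r | variance factor 1 − r² | residual SD | power for 17.7 points |
|---|---|---|---|
| 0 (unadjusted) | 1.00 | 29.0 | 0.81 |
| 0.1 | 0.99 | 28.9 | 0.81 |
| 0.3 | 0.91 | 27.7 | 0.84 |
| 0.5 | 0.75 | 25.1 | 0.90 |
| 0.7 | 0.51 | 20.7 | 0.98 |

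**Step 4: the other reading of the SD.** If 29.0 is the SD of the change, and the SD is equal at both visits, the SD of the 52-week score is 29.0/√(2(1 − r)). At r = 0.3 this is 24.5. Unadjusted power is then 0.92, and adjusted power is 0.94 (residual SD 24.5 × √0.91 = 23.4). At r = 0.5 the two readings coincide (0.81 and 0.90). The starting level depends on the reading, but the variance factor 1 − r² does not.

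**Step 5: does the conditional adjustment help?** It lists delivery and adherence, duration of participation, surgical procedures and postoperative physiotherapy. All of these arise after randomisation. Baseline score, age stratum and centre are not listed. Adjusting for what happens after allocation recovers none of the precision in Step 3, and it can bias the arm comparison where the treatment itself affects those factors.

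**The case against.** The strongest defence is that the planned test is sound. Comparing randomised arms at 52 weeks (FJS-12) or 6 weeks (Mod-PEI-2) is valid and addresses the aim. The sample size was built on that test, so it has its planned 80% power for 17.7 points. Leaving out the age stratum is conservative. The benefit of adjustment rests entirely on an r that the article does not report, and near zero it is negligible. The Abstract may mean that mixed models also serve the group comparison, and covariate lists are often left to an analysis plan. All of this stands, and it limits the point to efficiency and clarity. It does not remove the point, because the article does assign the methods, and it assigns the baseline-adjusted model to change within groups.

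Stronger readings are tempting, and the documents do not support them:

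- **That the trial's question goes unanswered.** This criticism fits only the within-group model. The t-test answers the question.
- **That only completers are analysed and patients lost to follow-up are simply discarded.** The article says this nowhere. It commits to intention-to-treat and promises suitable methods to account for missing data. The sentence that "a sensitivity analysis will be performed to quantify the magnitude of missing data from patients lost to follow-up" is loosely worded, but the next one covers the handling of missing outcomes.
- **That framing the sample size as a difference from baseline to 52 weeks contradicts a test of follow-up scores.** Under randomisation the expected arm difference is the same for both.

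**Conclusion.** The point holds as one of efficiency and clarity. The between-group test named in the Analysis plan is valid, but it uses neither the baseline score nor the age stratum. The baseline-adjusted model is attached to a comparison that is not randomised, and the conditional adjustment is no remedy. Abstract and Analysis plan need to be reconciled on this.

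A reader might infer that the sample size is wrong or that the trial is underpowered because of this choice. That does not follow, since 110 reproduces exactly from the unadjusted test.

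The size of the gain is uncertain. It ranges from nothing at r near zero to 9 percentage points of power at r = 0.5 (0.81 to 0.90) and 17 at r = 0.7 (0.81 to 0.98). These figures assume 44 evaluable patients per arm, a two-sided 5% level, and that 0.61 refers to the SD of the 52-week score.

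**What to change.** Name one primary between-group analysis for each primary outcome and state it alike in the Abstract and the Analysis plan.

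- **FJS-12:** ANCOVA at 52 weeks, or a mixed model with arm, visit and arm-by-visit. Include the baseline score and age stratum as covariates, and centre if wished. Report the adjusted arm difference at 52 weeks with its 95% confidence interval. In the mixed model, do not enter baseline both as an outcome visit and as a covariate.
- **Mod-PEI-2:** the sample size rests on the proportion scoring above 21 at 6 weeks (0.6 against 0.3). If that remains the endpoint, use a logistic or binomial model with the same covariates. If the total score is meant, use the FJS-12 approach at 6 weeks and say so.
- **Within-group change:** present as description, not as evidence of effect.
- **Adjustment for delivery, adherence, surgery and postoperative physiotherapy:** keep separate from the primary analysis and label as exploratory.

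The cost is a few sentences and modest programming in the planned software. The baseline data are already collected. Recruitment is expected to continue throughout 2026 and data collection until the end of 2027, so the wording can still be fixed before the final data are available.

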### Other measures

#### Adherence

Adherence to the intervention is recorded using an exercise journal maintained by the physiotherapist overseeing the intervention. Patients’ attendance and participation in each session are documented, along with the education topics discussed with each patient during every session. The journal tracks the number of exercises performed, variation of exercises, dosage and load used and the SANE score for each patient at every session. Educational topics discussed are recorded individually for all patients, although the detailed content of these discussions is not documented. Patients without a scheduled surgery date after the 8-week intervention who choose to continue exercise therapy, either supervised or unsupervised, maintain an identical exercise journal and record their own sessions. To support continued adherence, check-ins by phone or video conference with the physiotherapist in charge are scheduled every other week, as previously described.

For patients assigned to standard care, any participation in ongoing exercise interventions outside the trial is recorded using patient-reported forms at baseline and at the 8-week and 1-week pre-surgery follow-ups. This includes the type of exercise performed, its duration and weekly frequency. Participation in the standardised preoperative education session is also documented.

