## Discussion

### Strengths and limitations

Strengths of this trial include the following: (1) concealed, stratified randomisation to reduce the risk of allocation bias; (2) supervised exercise therapy, allowing easy monitoring of exercise technique, dosage and progression; (3) blinded assessors of objective outcomes to reduce the risk of detection bias; (4) multicentre design to increase external validity; (5) individualisation of total exercise number and variations, enabling tailored exercises and promoting person-centred care; (6) intervention delivered in a group format, offering peer support; (7) combination of exercise therapy and patient education according to recommendations, improving functional performance and creating realistic expectations among patients awaiting TKR; and (8) opportunity to ask individual questions and engage in discussion with physiotherapists experienced in preoperative and postoperative rehabilitation of TKR.

Limitations of this trial include the following: (1) waiting time to surgery will differ between patients, resulting in variable total exposure time and challenges for statistical analysis; (2) the combined intervention design does not allow differentiation between the effects of exercise therapy and patient education; (3) on-site intervention delivery at a set time in the afternoon may exclude patients with long travel distances and make participation difficult for working-age patients or those with other commitments; (4) individualisation of exercise therapy and patient education may limit comparability with other studies and generalisability of results, although individualisation is performed within predetermined boundaries; (5) patients’ expectations may increase as a result of the intervention, potentially raising the risk of dissatisfaction if expectations are not fulfilled; (6) satisfaction is a multifactorial concept and challenging to assess comprehensively^59 60^; and (7) the trial coordinator (primary investigator) and statistician are not blinded to group allocation.

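### The plan lets primary and secondary outcome analyses be adjusted for adherence, postoperative physiotherapy and other post-randomisation variables, without saying which result is primary

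*Protocol article*

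**What the plan says.** The Analysis plan first sets out a between-group comparison by arm: primary and secondary outcomes "at each follow-up assessment will be analysed using independent samples t-tests or non-parametric equivalent tests". It names two analysis populations, "applying intention-to-treat and per-protocol approaches with an α-level of 0.05". After a sentence on predictor regressions, it adds that the same outcome analyses "will be adjusted, if necessary, for differences in intervention delivery and adherence, duration of participation, surgical procedures and postoperative physiotherapy care".

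Three other places bear on this:

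- **Randomisation:** "Allocation is performed by the trial coordinator immediately after the baseline assessment". Everything in the adjustment list therefore comes later.
- **Adherence:** "Adherence to the intervention is recorded using an exercise journal maintained by the physiotherapist overseeing the intervention". For the control arm, a different instrument is used: "any participation in ongoing exercise interventions outside the trial is recorded using patient-reported forms at baseline and at the 8-week and 1-week pre-surgery follow-ups".
- **Strengths and limitations:** the protocol declares that "the trial coordinator (primary investigator) and statistician are not blinded to group allocation".

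**The concern.** An intention-to-treat comparison estimates the effect of being allocated to prehabilitation on top of standard care, and randomisation protects it. A covariate that allocation itself changes, or that stands in for allocation, breaks that protection. The arm coefficient then answers a different question, and its error can go in either direction.

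The sentence applies to the primary outcomes (FJS-12 and Mod-PEI-2) and is not limited to per-protocol, sensitivity or exploratory use. It gives no criterion for when adjustment is needed, and no order of precedence if the unadjusted and adjusted results disagree. With a statistician who knows the allocation, the choice between two results could be made after both have been seen.

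**Working it through.** **1. The plan's own figure.** The Sample size section targets 110 patients. A two-sample t-test at effect size 0.61, two-sided 5% level (sidedness assumed) and 80% power needs 44 per arm, so 88 in total; 88 / (1 − 0.20) = 110. The figure reproduces. It rests on an unadjusted comparison, so nothing below changes it.

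**2. When each covariate is realised, and whether arm can affect it.**

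| Covariate | Where recorded | Can allocation affect it? |
|---|---|---|
| Delivery and adherence | Exercise journal, during the 8 weeks and up to surgery (Adherence) | Yes, by construction: trial sessions exist only in the prehabilitation arm |
| Postoperative physiotherapy | 6, 12 and 52 weeks after surgery (Description of surgical procedures and postoperative physiotherapy) | Plausibly: it continues according to individual goals and need (Standard care), and the Introduction gives better recovery and less unnecessary healthcare use as aims of prehabilitation |
| Duration of participation | Follows from waiting time (Data collection and blinding; Strengths and limitations) | Waiting time exists in both arms; no passage says allocation alters surgery scheduling |
| Surgical procedures | Surgery report | No passage suggests that it does |

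**3. Why the last column decides the matter.** In linear regression, adding a covariate M to a model with arm gives exactly

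adjusted arm effect = unadjusted arm effect − (difference in mean M between arms) × (within-arm slope of outcome on M).

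If allocation does not affect M, the mean difference is zero in expectation and nothing is lost. If it does, the estimate moves.

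**4. Illustration with assumed coefficients (not trial figures).** The true total effect is 0.60 throughout. In the first three rows arm shifts M by 0.5.

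| Scenario | Within-arm slope | Adjusted effect |
|---|---|---|
| M is a mediator: direct effect 0.30, M on outcome 0.6 | 0.6 | 0.60 − 0.5 × 0.6 = 0.30 |
| M has no effect on outcome but shares an unmeasured cause (0.5 on each; residual variance of M is 1) | 0.5 × 0.5 / (0.5² + 1) = 0.2 | 0.60 − 0.5 × 0.2 = 0.50 |
| Both | 0.6 + 0.2 = 0.8 | 0.60 − 0.5 × 0.8 = 0.20 |
| Arm does not affect M | any | 0.60 − 0 = 0.60 |

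A simulation of 2 million records per scenario gave 0.30, 0.50, 0.20 and 0.60. The unadjusted estimate was 0.60 each time.

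**5. Adherence.** If session attendance is used and controls are coded zero, the mean difference is the average attendance itself, which cannot be near zero in a delivered intervention. The slope then comes only from comparing better with worse attenders within the prehabilitation arm, which is not a randomised comparison. The arm coefficient becomes the contrast for a patient allocated to prehabilitation who attends nothing.

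In a separate simulation with assumed average attendance of 75% linked to a prognostic trait, the correlation of arm with adherence was 0.934. The variance inflation is 1 / (1 − 0.934²) ≈ 7.8. The estimate moved from 0.299 to −0.662, which requires a within-arm slope of (0.299 + 0.662) / 0.75 ≈ 1.28 SD from no attendance to full attendance. That is a steep assumption. The example shows the mechanism, not a likely size.

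**The case against.** **Timing alone does not bias.** A reader might infer that, because all the listed variables arise after randomisation, any adjusted estimate is biased. The documents do not support that. Type of replacement, patellar resurfacing and extra soft tissue procedures are not described as responding to prehabilitation, and waiting time is not described as depending on arm. This objection stands, and it limits the point to delivery and adherence and, more tentatively, to postoperative physiotherapy.

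**Adherence need not be empty in controls.** The protocol records outside exercise and attendance at the standard education session for control patients, and the Analysis plan does not say which measure would be used. A common measure of exercise in both arms would be less collinear with arm than session attendance. That is fair. Such a measure would still be expected to differ by arm because of the intervention, so the formula above would still apply.

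**An unadjusted comparison is already planned.** It comes first in the Analysis plan, and the adjustment can be read as supplementary. A reader might therefore infer that the primary comparison is lost; it is not, and the unadjusted test remains valid. But no sentence makes it the primary result.

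**A fuller analysis plan may define the trigger, and the lack of blinding is declared.** Both are true. The finding does not rest on a missing criterion, however: the rule as stated names adherence and postoperative physiotherapy as adjusters for the primary outcomes.

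**The shifts may be small.** In one assumed example with a physiotherapy variable and no true mediation, the estimate moved from 0.308 to 0.257. That is 0.05 SD, against a standard error of √(2/44) ≈ 0.21 SD at 44 per arm. The size in this trial is unknown.

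**Conclusion.** The point holds in graded form. Adjusting for delivery or adherence would distort the arm effect. Adjusting for postoperative physiotherapy may remove part of the effect or open collider bias. Surgical procedure and waiting time would bias little or not at all, provided allocation does not affect them. An estimate adjusted for adherence, or for physiotherapy that arm has changed, is not the intention-to-treat effect.

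The unadjusted comparison is sound. The weakness is that the plan does not rank it above the adjusted one, leaves the trigger undefined and has the analysis done with allocation known, so the choice between results is open to the data. No size can be given for this trial: the 0.20 to 0.60 range and the sign reversal in the adherence example rest on assumed coefficients.

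**What to change.** In the Analysis plan:

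- Name the intention-to-treat comparison by allocated arm as the primary result, adjusted only for baseline variables fixed in advance: the baseline score where collected, age stratum and centre.
- State that this result is not adjusted for delivery or adherence, duration of participation, surgical procedures or postoperative physiotherapy.
- Report those four by arm descriptively.
- Confine any model using them to analyses labelled exploratory. For adherence, one option is a complier-average effect with randomised arm as the instrument, stating the assumption that allocation acts on the outcome only through the prehabilitation received.

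The sentence need not be removed altogether; relabelling these analyses and naming the primary result is enough. The cost is wording only, and sample size and data collection are unchanged. Data collection is expected to run to the end of 2027, so the change can be made and dated before the analysis.

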**Methods and analysis:**

This multicentre, randomised controlled parallel-group trial is planned to be conducted within two specialised orthopaedic outpatient rehabilitation units in the southeast healthcare region of Sweden. Eligible patients (40–85 years, awaiting unilateral TKR) are randomised 1:1, stratified by age (≤67, >67 years), to either 8 weeks of prehabilitation—comprising two times per week supervised exercise therapy (strength, range of motion and balance) and education—in addition to standard care, or to standard care alone. Standard care consists of self-care, a single standardised preoperative education session and standardised postoperative rehabilitation. Assessments are conducted at baseline, post-intervention, 1 week pre-surgery and 6, 12 and 52 weeks post-surgery. A total of 110 patients will be recruited to the trial. Primary outcomes are joint awareness (Forgotten Joint Score-12) and patient enablement (modified Patient Enablement Instrument-2). Secondary outcomes are patient satisfaction (5-category Likert scale), the Knee injury and Osteoarthritis Outcome Score, the EuroQol 5 Dimension 3 Level questionnaire, the International Physical Activity Questionnaire—short form, objective function and accelerometer-based physical activity. Analyses will follow intention-to-treat and per-protocol principles. Between-group and within-group differences will be tested using t-tests or non-parametric equivalents, and linear mixed models or generalised linear models. Multiple linear regression and logistic regression will be used to analyse predictor variables for the primary outcomes. Sensitivity analyses will be performed to quantify the magnitude of missing data from patients lost to follow-up.

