The aim of this trial is to investigate the effect of adding prehabilitation to standard care before TKR, compared with standard care alone, focusing on (1) patient-reported joint awareness 1 year after TKR, and (2) patient enablement and objectively measured knee function 6 weeks after TKR.

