30s CST	X	X	X	**X**		
activPAL accelerometer	X	X			X	X

Bold crosses are considered main outcome time points.

EQ5D-3L, EuroQol 5 Dimension 3 Levels; FJS-12, Forgotten Joint Score-12; IPAQ-sf, International Physical Activity Questionnaire-short form; KOOS, Knee injury and Osteoarthritis Outcome Score; Mod-PEI-2, modified Patient Enablement Instrument 2; postop, postoperation; preop, preoperation; ROM, range of motion; 30s CST, 30 second Chair to Stand-Test; w, week.

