### Sample size

To detect a difference in the MIC of 17.7 points (effect size 0.61) and the MCID of 13.7 points between the SC+P and SC groups in the FJS-12^16^ from baseline to the 52-week follow-up, and assuming a 0.6 proportion of total scores >21 points for the Mod-PEI-2 in the SC+P group versus 0.3 in the SC group at the 6-week follow-up, a total of 110 patients is targeted for inclusion across the two groups (80% power, 5% α-level, with an estimated 20% dropout included).

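### The sample size gives each of the two primary outcomes a full 5% alpha, while the analysis plan calls for alpha adjustment without exempting them; under Bonferroni over the two, power is about 72–73%, not 80%

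*Protocol article*

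**What the plan says.** The Abstract (Methods and analysis) names two primaries: "Primary outcomes are joint awareness (Forgotten Joint Score-12) and patient enablement (modified Patient Enablement Instrument-2". Table 3 places their main time points at 52 weeks and 6 weeks after surgery respectively.

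The Sample size section rests on both. For FJS-12 it says "To detect a difference in the MIC of 17.7 points (effect size 0.61"), and it adds "the MCID of 13.7 points between the SC+P and SC groups in the FJS-12". For Mod-PEI-2 it says "assuming a 0.6 proportion of total scores >21 points for the Mod-PEI-2 in the SC+P group versus 0.3 in the SC group" at 6 weeks. The target of 110 carries the terms "80% power, 5% α-level, with an estimated 20% dropout included". No division of alpha between the two outcomes is mentioned, and sidedness is not stated.

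The Analysis plan sets an alpha of 0.05 overall and then adds: "Multiple analyses will be performed using α-level adjustment methods, such as the Bonferroni method". It does not say which tests are adjusted together, and it does not leave the two primaries out.

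**The concern.** Power is a property of a test at a given alpha. The Sample size section promises 80% using the whole 5% for each primary outcome. The Analysis plan describes a rule that, read plainly, would reduce that alpha. Both cannot hold for the same test.

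There is a cost either way. If the primaries are adjusted by the method the protocol names, each has less power than stated. If they are not, two primaries at 5% each carry a combined false-positive risk well above 5%, and the adjustment would protect only the lesser outcomes. Left open, the choice could also decide whether a primary result with a p-value between 0.025 and 0.05 is called significant.

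**Working it through.** **Inputs (all from Sample size unless noted).** FJS-12 effect size d = 0.61 for 17.7 points; Mod-PEI-2 proportions 0.6 and 0.3; power 80%; alpha 5%; dropout 20%; N = 110; allocation 1:1 (Randomisation). Assumption: two-sided tests.

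**Step 1: reproduce 110.**
- FJS-12: n per arm = 2(z₀.₉₇₅ + z₀.₈₀)²/d² = 2(1.960 + 0.842)²/0.61² = 42.2, so 43. The t-test version gives 43.2, so 44 per arm and 88 in total; 88/0.8 = 110 exactly.
- Mod-PEI-2, with pooled proportion 0.45: n per arm = [1.960√(2·0.45·0.55) + 0.842√(0.6·0.4 + 0.3·0.7)]²/0.3² = 42.0, so 42 per arm and 84 in total; 84/0.8 = 105. FJS-12 therefore sets the N.
- A one-sided 5% would need only 34 and 33 per arm, which does not give 110.

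**Step 2: could 110 already contain a split?** At 0.025, z₀.₉₈₇₅ = 2.241.
- FJS-12: 52 per arm (t-test 53), which is 130 to 134 recruited depending on method and rounding.
- Mod-PEI-2: 51 per arm, or 128 recruited.

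So it could not; 110 uses the unsplit 5%.

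**Step 3: power with 44 per arm.**

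| Alpha per test | FJS-12, 17.7 points (t-test) | Mod-PEI-2, 0.6 v 0.3 |
|---|---|---|
| 0.05 | 80.8% | 81.9% |
| 0.025 | 71.8% | 73.1% |

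The normal approximation for FJS-12 gives 81.6% and 73.2%. For example, 0.61·√(44/2) − 2.241 = 0.620, and Φ(0.620) = 0.732.

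**Step 4: no adjustment.** Two independent tests at 0.05: 1 − 0.95² = 0.0975, about 9.8%.

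**Step 5: Holm over the two primaries**, both assumed effects true and tests independent. An outcome is significant if its p-value is at or below 0.025, or lies between 0.025 and 0.05 while the other's is at or below 0.025.
- FJS-12: 0.718 + (0.808 − 0.718)·0.731 = 0.784.
- Mod-PEI-2: 0.731 + (0.819 − 0.731)·0.718 = 0.794.

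A simulation for FJS-12 with correlation between outcomes from 0 to 0.5 gave 0.78 to 0.79.

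The 13.7-point FJS-12 difference is not used here, because 110 does not follow from it: at the implied SD (17.7/0.61 = 29.0), 44 per arm gives about 59% even at an unadjusted 5%. That is a separate matter.

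**The case against.** The strongest reply is that the text does not commit the trial to a Bonferroni split of the primaries. The Analysis plan gives Bonferroni as an example and names no family. The preceding paragraph plans comparisons at every follow-up, so the adjustment may be meant for repeated visits or secondary outcomes. The primaries would then keep 0.05 and the power shortfall would vanish. This stands, and it makes the shortfall conditional. It does not remove the disagreement, because that reading leaves the roughly 9.8% error of Step 4.

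A second reply is that the family is normally defined in the statistical analysis plan. That is fair, and the missing definition is not the point here. The point is that the article states a power and a rule that do not fit together; a later plan would have to revise one or narrow the other.

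Third, success might require both primaries, in which case each keeps 0.05. No section says so. The chance of success would then be about 0.808 × 0.819 = 66% if the tests are independent.

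Fourth, the loss is modest. Holm is compatible with the protocol's wording. Under plain Bonferroni the chance of detecting at least one of the two effects is 1 − 0.282 × 0.269 = 92% (independent tests, both effects true). With no dropout at all (55 per arm), power at 0.025 is 82% and 83%. All of this stands and bears on severity.

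A reader might also infer something stronger: that alpha is shared over the five bold-marked outcomes in Table 3, or over every outcome at every visit, with power far below 70%. The documents do not support this. The table note says "Bold crosses are considered main outcome time points", which marks time points and does not define a testing family. The aim does name "patient enablement and objectively measured knee function 6 weeks after TKR", but the outcome sections list objective function as secondary, and a secondary outcome may have a main time point. No section pools secondary tests with the primaries.

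**Conclusion.** The concern holds in conditional form. The Sample size and Analysis plan sections do not agree on the alpha for the two primary outcomes. If Bonferroni is applied over the two, power is 8 to 9 percentage points below what each has at 5%, and below the stated 80%. If they are left unadjusted, the stated power stands, but two-outcome error control at 5% does not.

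This rests on two-sided tests, the protocol's own effect sizes, and the planned 20% dropout actually occurring. It would be too strong to say that the trial is underpowered as it stands, because the article does not settle whether the primaries are adjusted. The arithmetic behind 110 is sound. This is an inconsistency between sample size and multiplicity rule that should be fixed, of moderate importance because a better procedure recovers most of the loss.

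**What to change.** State in the Analysis plan that the confirmatory family consists of exactly two tests, FJS-12 at 52 weeks and Mod-PEI-2 at 6 weeks, tested with Holm at an overall 5%. Holm gives the same family error control as Bonferroni and is never less powerful. State that all other outcomes and visits are secondary and lie outside that family.

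In the Sample size section, state that the tests are two-sided (if so) and restate power for 110 recruited and 44 evaluable per arm: about 72–73% per outcome under Bonferroni, or about 78–79% under Holm if both assumed effects hold.

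The cost is wording and a slightly less favourable stated power. No extra patients are needed. The protocol expects recruitment through 2026 and data collection to the end of 2027, so the rule can be fixed before outcome data are complete.
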